### Objectives

The primary objective of this study is to evaluate whether the deployment of the gamified version of the Jooay App is associated with changes in app engagement compared with the previous nongamified version. Specifically, we will examine changes in app engagement following the deployment of the gamified Jooay App, using an interrupted time series (ITS) analysis of aggregated app analytics data.

The secondary effectiveness and feasibility objectives are to examine changes in specific engagement indicators, including app sessions, active users, duration of use, frequency of use, and use of key app features; to evaluate the feasibility of the gamified Jooay App among youth with disabilities, parents, and clinicians; and to explore postdeployment participation-related outcomes, including planned activities, attended activities, satisfaction, and perceived achievement.

The implementation objectives are to assess the process of implementing and scaling up the gamified Jooay App across participating Canadian provinces; to describe the expansion, role, and activities of the Jooay KB networks across these provinces; to identify provincial barriers and facilitators influencing app uptake, implementation, and sustainability; and to examine how the app and KB networks support the identification of community-based play and leisure opportunities for children and youth with disabilities.

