Following the completion of the pilot feasibility study, the gamified version of the app will be deployed to all users at the community level. The date of deployment of the gamified version will serve as the intervention point for an ITS analysis. This design was selected because gamification will be introduced at the app or community level and cannot be randomized across users once it is deployed. The ITS design will allow us to examine whether the introduction of the gamified version is associated with changes in the level and/or trend of engagement outcomes compared with patterns observed during use of the previous nongamified version. Engagement data will be extracted from in-app analytics and aggregated at monthly intervals. The preintervention segment will include monthly data from the previous nongamified version of Jooay, and the postintervention segment will include monthly data after deployment of the gamified version. We will include a minimum of 12 monthly time points before and 12 monthly time points after deployment to allow the estimation of baseline trends, postintervention changes, and seasonal patterns. Seasonality will be assessed through visual inspection of monthly trends. If seasonal patterns are identified, models will include calendar month indicators. We will also document other major app updates, holidays, school calendar periods, or external events that may influence engagement and consider these in adjusted or sensitivity analyses. Engagement outcomes will be measured using both backend and frontend indicators. Backend engagement measures will include app usage frequency, number of accesses, duration of use, and feature usage as captured through in-app analytics. Frontend engagement measures will include engagement with community-based features for youth users and the inclusion of community play and leisure activities within intervention plans developed by clinicians and educators. Additionally, following the deployment of the gamified version, participation in leisure will be assessed using newly co-designed in-app features that capture the number of activities users plan and attend, as well as users’ self-reported satisfaction and perceived achievement. These outcomes will be examined descriptively and longitudinally during the postintervention period to explore patterns of participation over time and their association with app engagement.

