###### Participation

Participation’s attendance and involvement will be assessed using the “Activity Planner” and “My Summary” features within the Jooay App. The “Activity Planner,” a gamification feature, will allow users to track their planned leisure activities and monitor their completion rates. This feature provided insights into users’ engagement in planned leisure activities over the course of the study. The “My Summary” feature stored users’ responses to self-assessment questionnaires, in which they reflected on their experiences after participating in a specific leisure activity. Users expressed their feelings about the activity by selecting an emoji and identified the benefits gained by choosing relevant domains from the F-word framework for childhood development [28].

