### Community Level

The effectiveness of the gamification-based mobile app intervention will be assessed primarily through user engagement metrics collected through app analytics, including the number of clicks, logins, active time spent, access frequency of individual gamification features, comments, and reviews. These data will provide insights into how youth, caregivers, and professionals interact with the app over time. Additionally, differential outcomes will be examined for health care and education professionals, focusing on the integration of community participation into intervention plans and health promotion strategies. For youth, the impact of the intervention will be evaluated based on increased participation in community activities, collected from the “Activity Planner” and “My Summary” features within the Jooay App.

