##### Community Level

Engagement will be measured using a segmented linear regression model to analyze changes over time, including preintervention trends, immediate changes before and after the intervention, and postintervention trends. Where appropriate, models will account for autocorrelation, seasonality, and nonindependence of repeated observations over time. App usage data will capture time spent and interactions with gamification features, with descriptive statistics assessing usage patterns by province, disability, and age among youth participants. Outcomes available only in the gamified version, including planned and attended activities, satisfaction, and perceived achievement, will be analyzed descriptively and longitudinally during the postintervention period rather than included in the primary ITS comparison.

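### Post-deployment participation trends come only from users who keep logging in the app, so they can drift up or down with no change in any user, yet they are to be used to judge impact on youth

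*Protocol article*

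**What the plan says.** All statements are in the protocol article.

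- **Source of the data.** Under Procedures, Effectiveness, after deployment "participation in leisure will be assessed using newly co-designed in-app features that capture the number of activities users plan and attend", together with self-reported satisfaction and perceived achievement.
- **When a score exists.** Under Variables and Outcomes, Participation, the My Summary feature "stored users’ responses to self-assessment questionnaires, in which they reflected on their experiences after participating in a specific leisure activity". A score therefore needs both attendance and a later entry in the app.
- **Analysis.** Procedures, Effectiveness: "These outcomes will be examined descriptively and longitudinally during the postintervention period to explore patterns of participation over time". The same sentence adds their association with app engagement. Analysis, Community Level, says that these outcomes "will be analyzed descriptively and longitudinally during the postintervention period rather than included in the primary ITS comparison", because they exist only in the gamified version.
- **Status.** Objectives lists them among the secondary aims, "to explore postdeployment participation-related outcomes, including planned activities, attended activities, satisfaction, and perceived achievement".
- **Use.** Variables and Outcomes, Community Level: "For youth, the impact of the intervention will be evaluated based on increased participation in community activities", with the data taken from the Activity Planner and My Summary.
- **Population.** Variables and Outcomes, Implementation, makes growth in the number of app users an outcome, so the user base is open.
- **Data handling.** Ethical Considerations has the app analytics analysed in aggregate and de-identified.

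**The concern.** Someone who leaves the app, or who keeps attending activities but no longer logs them, disappears from every one of these measures. An activity that was planned and never updated could mean that the user did not attend, or that the user attended and did not return to the app. Those who remain, plus those who have just joined, make up each later month's data.

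This would matter little if the outcomes only described use of the new features. However, the Community Level section evaluates impact on youth by increased participation. These features have no pre-deployment values, so an increase can only be one within the post-deployment months, and that is the contrast that changing composition distorts. A shift in who logs could then be reported as a change in participation. The planned association with app engagement has a related weakness: both sides are recorded through app use, so part of the association is built in. The limitations under Methodological Considerations mention backend metrics for engagement and generalizability, but not selective logging of participation.

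**Working it through.** The documents give no attrition rate, logging rate or score distribution for these outcomes, so there is no stated figure to reproduce. The check asks whether composition alone can move the trend, in which direction, and by how much.

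**Input from the protocol.** The post-deployment segment: "We will include a minimum of 12 monthly time points before and 12 monthly time points after deployment". This is stated for the interrupted time series (ITS) and is used here as the follow-up length. Month 1 to month 12 is 11 intervals.

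**Assumed inputs.** Each user has a fixed score 3.5 + 0.8z, with z standard normal, so no user changes. The monthly probability of stopping is h(z) = logistic(logit(p) + ln(OR)·z), where p is stopping at the mean score and OR is the odds ratio per SD of higher score.

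**Formula, no new users.** The share still logging at month 12 is S = E[(1 − h(z))^11]. The drift in the mean score is 0.8 · E[z(1 − h(z))^11] / S.

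| p | OR | Still logging | Drift (points) | Drift (SD) |
|---|---|---|---|---|
| 0.10 | 0.67 | 31.9% | +0.32 | +0.40 |
| 0.10 | 1.0 | 0.90^11 = 31.4% | 0 | 0 |
| 0.10 | 1.5 | 32.0% | −0.32 | −0.40 |
| 0.05 | 0.8 | 56.6% | +0.10 | +0.12 |
| 0.20 | 0.5 | 13.4% | +0.77 | +0.96 |

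The last two rows bound the rise when lower scorers stop more often. Inverting the odds ratio reverses the sign.

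**Formula, open user base.** Each month the stoppers are replaced by new users drawn from the starting distribution. At p = 0.10 and OR 0.67 the drift falls from +0.32 to about +0.19. At p = 0.20 and OR 0.5 it falls from +0.77 to about +0.35.

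**Independent simulation.** 200,000 users had fixed satisfaction (mean about 3.5) and a fixed activity rate (mean 2 per month). At 15% monthly stopping without new users, the results from month 1 to month 12 were as follows.

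| Who stops | Mean satisfaction, active users | Activities per active user | Total activities per original user |
|---|---|---|---|
| Unrelated to score | 3.49 to 3.49 | 2.00 to 2.00 | 2.00 to 0.34 |
| Low scorers more (logit slope 0.5 per SD) | 3.49 to 4.00 | 2.00 to 2.33 | 2.00 to 0.45 |
| High scorers more (same slope, reversed) | 3.49 to 2.96 | 2.00 to 1.68 | 2.00 to 0.32 |

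The choice of summary therefore matters as much as the stopping pattern. In the second row the rate per active user rises while the total falls, although no user has changed.

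**The case against.** The strongest reply has four parts.

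1. **Status and detail.** The outcomes are exploratory and outside the primary ITS comparison. Cohort definitions, denominators and the handling of users who stop are details that an article commonly leaves to a fuller protocol or analysis plan. A longitudinal description does not rule out within-user analysis, and nothing says that averages of active users will be tracked or that unlogged plans will count as not attended. This largely stands and limits the severity. It does not cover the statement on youth impact, which the article itself makes and which goes beyond exploration.
2. **Direction.** A reader might infer that scores will rise because users who benefit less leave first. The documents do not support this: nothing in them links stopping to satisfaction. A rise needs lower scorers to stop more often and a summary per active user. Otherwise the mean can stay flat or fall, and totals of logged activities tend to fall unless new users offset the losses.
3. **Scope.** A reader might also infer that these are the study's only participation measures. They are not. The pilot's closing survey asks about perceived impact on leisure participation, and its interviews are analysed for participation satisfaction. Neither depends on continued planner entries. The in-app features are, however, the measures named for impact on youth at community level.
4. **Visibility.** Active users are a listed engagement indicator, so overall attrition would be partly visible. It would not show whether those who left differed from those who stayed.

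**Conclusion.** The concern holds in a limited form. Post-deployment trends in these outcomes combine within-user change with changing composition and can drift in either direction with no individual change. Under assumed 10% monthly stopping and a score SD of 0.8, the 12-month drift is about +0.32 points at an odds ratio of 0.67, 0 at 1.0 and −0.32 at 1.5. It is smaller, about +0.19 at 0.67, when new users replace stoppers. These sizes illustrate the mechanism and are not predictions for this app.

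Severity is modest and the primary ITS comparison is unaffected. The point deserves action because a trend that can move either way without any user changing cannot carry the impact statement for youth.

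**What to change.** - **Cohort.** In Procedures, Effectiveness, and Analysis, Community Level, analyse these outcomes by cohort of first planner use, with all starters as the denominator.
- **Visibility.** Report the number and share still logging each month beside every score.
- **Change.** Estimate change within user, comparing later scores with that user's own first scores, rather than from averages of whoever is active.
- **Unresolved plans.** Class planned activities with no later app use as outcome unknown, and show completion rates with these counted both ways.
- **Interpretation.** Align the youth impact statement in Variables and Outcomes, Community Level, with the exploratory status in Objectives and Procedures, so that a trend among active loggers is not read as impact.

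**Cost.** A little more analysis and a possibly less favourable trend. Within-user change needs a pseudonymous user key in the de-identified data, with results still reported in aggregate as Ethical Considerations requires. The article does not say that the analytics hold first-use dates or such a key, so this should be confirmed. According to Results, the ITS study and data analysis had not begun at submission, which leaves room to settle the wording beforehand.

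### Youth impact is to be judged by increased participation, but the in-app participation outcomes have no baseline or comparator, and a rise within the short post-deployment series cannot be told from season

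*Protocol article*

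**What the plan says.** All references are to the protocol article.

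- **Objectives:** planned activities, attended activities, satisfaction and perceived achievement are listed among the secondary objectives, to be explored after deployment.
- **Procedures, Effectiveness:** these outcomes come from new in-app features and will be "examined descriptively and longitudinally during the postintervention period to explore patterns of participation over time", together with their association with app engagement.
- **Analysis, Effectiveness, Community Level:** "Outcomes available only in the gamified version, including planned and attended activities, satisfaction, and perceived achievement, will be analyzed descriptively and longitudinally". The same sentence keeps them out of the main ITS contrast.
- **Variables and Outcomes, Community Level:** for youth, "the impact of the intervention will be evaluated based on increased participation in community activities", with Activity Planner and My Summary named as the source.
- **Length of series (Sample Size; Procedures, Effectiveness):** "We will include a minimum of 12 monthly time points before and 12 monthly time points after deployment". Data collection is expected from March 2026 to June 2027 (Results), and deployment follows completion of the pilot.
- **Season:** visual inspection, and then "If seasonal patterns are identified, models will include calendar month indicators". This is written for the engagement outcomes in the interrupted time series (ITS). No equivalent is stated for the participation outcomes.

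**The concern.** Three places treat the in-app participation outcomes as exploratory or descriptive, and one of them keeps these outcomes out of the ITS comparison because the earlier app did not record them. A fourth makes an increase in the same outcomes the basis for judging the intervention's impact on youth.

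An increase needs something to increase from. With no pre-deployment measurement and no comparison group, the only candidate at community level is a rise across the post-deployment months. That rise would mix any real change with the time of year, and the release date would help decide whether it came out as a rise or a fall. At stake is whether the trial reports an effect on youth participation, the behaviour the app is meant to promote, from data that cannot show one.

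**Working it through.** **1. Is there a baseline or comparator?** The Analysis section says these outcomes are available only in the gamified version, so no pre-deployment values exist. The gamified version goes to all users at deployment, so no concurrent group is without it. The planned association with engagement is a comparison within the post-deployment period and supplies neither.

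**2. How long is the post-deployment series?** The guaranteed minimum is 12 monthly points, so each calendar month is seen once. March 2026 to June 2027 inclusive is 10 + 6 = 16 months. Deployment comes after the pilot, so 16 is an upper bound for the post-deployment part of that window. Two annual cycles need 24.

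**3. Can a trend be separated from season?** Apply the article's own season method (calendar-month indicators) to a post-only series: intercept + linear trend + 11 indicators = 13 parameters.

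| Post-deployment months | Rank of design | Residual df | Trend estimable? |
|---|---|---|---|
| 12 | 12 | 0 | No |
| 13 | 13 | 0 | Yes, from 1 repeated month, with no error estimate |
| 16 | 13 | 3 | Yes, from 4 repeated months |
| 24 | 13 | 11 | Yes, from 12 repeated months |

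At 12 months the trend is an exact linear combination of the intercept and the month indicators.

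**4. How large could a purely seasonal rise or fall look?** The documents give no seasonal amplitude, so this is an illustration. Take a single yearly cosine of amplitude A, no true change, and a least-squares line through n monthly points. Let k be the month's distance from the middle of the window.

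- Largest absolute slope = A × Σ k·sin(2πk/12) / Σ k².
- For n = 12: Σ k·sin(2πk/12) = 23.18 and Σ k² = 143, so the largest slope is 23.18/143 = 0.162A per month. First to last month is 11 steps: 0.162 × 11 = 1.78A.
- The slope equals this maximum times the sine of the seasonal phase at the middle of the window, so it runs from −0.162A through 0 to +0.162A as the release date moves.
- If the peak falls exactly on a monthly point, the 12 release months give absolute changes of 0.46A, 1.26A or 1.72A, six upward and six downward. If the peak falls midway between two points, they give 0, 0.89A, 1.54A or 1.78A, with two release months at exactly zero.

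Range over all phases: 0 to 1.78A in either direction.

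| Assumed A (% of mean) | Apparent 12-month change with no true change |
|---|---|
| 10% | 0% to 18%, up or down |
| 20% | 0% to 36%, up or down |
| 30% | 0% to 53%, up or down |

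For n = 16, the same formula gives 9.21/340 = 0.027A per month, and × 15 steps = 0.41A at most, or about 8% at A = 20%. The artefact shrinks with a longer series, but 16 months is reached only if the pilot takes none of the window.

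**The case against.** The strongest reply is that the plan already limits these outcomes. The objectives say they will be explored, the procedures and analysis sections say they will be described, and they are kept out of the ITS comparison. No slope, trend test or first-to-last contrast is planned for them. A monthly series showing season and change together is what a descriptive analysis delivers, and its layout can be left to a fuller document. All of this stands. A reader might infer that the plan will fit a trend to these data and report it as an effect; the documents do not say so, and the slope figures above are an illustration rather than a planned result.

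A reader might also infer that season must always produce a sizeable false change. It need not: the result can be zero, depending on where the seasonal peak falls. The single cosine and the amplitude are assumptions. Nor does the article say that participation is seasonal; it says only that holidays, school periods and other events may influence engagement.

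A smooth seasonal term would make a trend estimable from 12 points, but only by assuming the shape of the season, and the article names month indicators instead.

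None of this removes the sentence in Variables and Outcomes, Community Level. It is not missing detail: it fixes an evaluation criterion that conflicts with the other three places, and no later model choice can supply the baseline.

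**Conclusion.** The point holds as a conflict between a stated impact criterion and the data available to meet it. The absence of a baseline and comparator is the root and follows from the text alone. Season is a further reason why a rise within the series would not be evidence: with 12 months and free month effects the trend is not estimable, and a purely seasonal series could show a change of 0 to about 1.8A either way (0% to 36% of the mean if A is 20%).

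The exact non-estimability rests on the guaranteed 12 months and on month indicators; the size rests on an assumed single yearly cycle. The point does not touch the primary engagement comparison, from which these outcomes are excluded, and it is no objection to describing them.

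**What to change.** Bring the youth sentence in Variables and Outcomes, Community Level, into line with the Objectives, Procedures and Analysis sections:

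- Remove impact and increase as the evaluation criterion for the in-app participation outcomes.
- Report planned and attended activities, satisfaction and perceived achievement per active user by calendar month, as a post-deployment description only.
- State that no increase in, or effect on, participation will be concluded from this series.

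A table by month of entry may be added as description. It should not be used to claim an increase: within a calendar month, time since first use is fixed by entry month, so comparing durations of use is comparing entry cohorts, and confounding by season is exchanged for confounding by cohort. Seeing the same calendar month twice would ease the season problem but would still provide no pre-deployment baseline.

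The cost is a change of wording and a simple tabulation, best made before deployment; the article says the ITS study has not begun. The trial gives up a youth participation impact claim that its data cannot support.
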